### Sample size {14}

The sample size was calculated (nQuery 8 software, version 8.6.1.0, Statistical Solutions Ltd, Cork, Ireland) based on the primary endpoint of the study. Assuming SSI rates of 4% and 16% for the experimental and the standard group respectively (OR=4.571), the one-sided z-test (Group Sequential test of two proportions) at the 2.5% significance level with a total of two looks at the data will have overall 80% power to show superiority of the experimental over the standard arm if the study includes at least 232 patients (116 patients per intervention group). The calculation is continuity corrected due to the expected low proportion in the experimental group. The results assume that the group sequential design has one interim sequential test for monitoring and sample size re-estimation (two total looks at the data including final analysis), which means that an interim analysis is planned after half of the patients have reached 30 days post-surgery. The O’Brien-Fleming spending function is used to determine the efficacy test boundary and the non-binding futility boundary. The group sequential test boundaries (Z scale) for the interim and the final analysis are as follows:

Upper efficacy bounds: 2.963 and 1.969

Futility bounds: 0.555 (non-binding) and 1.1969.

A drop-out rate of about 20% is expected in this study, based on experience from similar trials previously conducted within the CHIR-*Net* trial network. Therefore, a total of 290 patients (145 per intervention group) should be included in the study.

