## Statistical methods

### Statistical methods for primary and secondary outcomes {20a}

The intention-to-treat (ITT) set consists of all patients who received irrigation of the abdominal cavity before closure of the abdominal fascia with one of the study solutions. Analysis will be performed as randomized regardless of the actual intervention and regardless of any further medical or surgical treatments. The Per-Protocol (PP) set consists of patients treated according to protocol, excluding any major protocol violations. The PP set will be analysed as treated. The Safety (SA) set will consist of all patients in the ITT set, analysed as treated.

All primary and secondary analyses will be performed on the ITT set. Sensitivity analysis of the primary endpoint will be performed on the PP set. The SA set will be used for the safety analyses. The incidence of SSI within 30 days after surgery will be compared between the two study groups using the one-sided group sequential test of two proportions at the 2.5% significance level with a total of two looks at the data. The primary endpoint analysis will be performed on the ITT set. Since the ITT set includes all patients who were treated in the study regardless of any further medical or surgical treatments, it is expected, that the SSI rates 30 days post-surgery will be available for most patients. Nevertheless, it is possible that some patients do not reach the primary endpoint due to death, withdrawal of informed consent, loss to follow-up, or other unforeseen reasons. Patients who die before day 30 will be considered as having SSI at time of death regardless of the intervention group, unless SSI was documented earlier. All other missing primary endpoint data will be dealt with using multiple imputations based on binary logistic regression models including LOC, ASA, BMI, age, diabetes, type of surgery, duration of surgery, use of wound-edge protectors, and intraoperative changing of gloves.

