### Methods for additional analyses (e.g. subgroup analyses) {20b}

Since randomization will be stratified by LOC, supportive analysis of the primary endpoint will be performed using a binary logistic regression model with dependent variable SSI and covariates intervention group and LOC. In addition, the following parameters might influence the outcome, which is why they will be included as model covariates in an additional model:Operation-related risk factors: (a) type of surgery; (b) duration of surgery; (c) NNIS Risk Score, (d) use of wound-edge protectors; (e) intraoperative changing of gloves before skin closure; (f) presence of an enterostomy; (g) administration and timing of antibiotic prophylaxis;Patient-related risk factors: (g) BMI; (h) ASA score; (i) Age; (j) diabetes; (k) smoking; (l) alcohol abuse; (m) Charlson Comorbidity Index, (n) history of SSI; (o) history of radiotherapy; (p) history of chemotherapy, (q) days of hospitalization prior to surgery.

Supportive analysis of the primary endpoint will be performed on the ITT set using multiple imputations for any missing SSI values and on the PP set. Secondary endpoints will be analysed by intervention arm on the ITT set, using appropriate descriptive statistics. Any explorative statistical testing will be performed using a significance level of 5%. The assessment of safety will be based on the frequency of AE/SAE as defined in the protocol within the safety population consisting of all patients randomized into the study.

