### Methods in analysis to handle protocol non-adherence and any statistical methods to handle missing data {20c}

Multiple imputations will be used for missing primary endpoint data. All other data will be analysed on a complete-case basis.

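### The listed imputation predictors for missing SSI do not include the intervention group, so imputation as written dilutes the primary treatment difference by roughly the share of endpoints imputed

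*Protocol article*

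**What the plan says.** Under Statistical methods for primary and secondary outcomes {20a}, the primary analysis compares SSI proportions between the two groups on the ITT set. Missing endpoints are handled in two ways.

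- **Deaths:** "Patients who die before day 30 will be considered as having SSI at time of death regardless of the intervention group", unless an SSI was documented earlier.
- **All other missing endpoints:** "multiple imputations based on binary logistic regression models including LOC, ASA, BMI, age, diabetes, type of surgery, duration of surgery", with the list closing on "use of wound-edge protectors, and intraoperative changing of gloves".

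That makes nine predictors, all of them baseline or operative characteristics. The section on missing data {20c} adds none: "Multiple imputations will be used for missing primary endpoint data".

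The section on additional analyses {20b} runs the supportive models "on the ITT set using multiple imputations for any missing SSI values". There the treatment term is named: a "binary logistic regression model with dependent variable SSI and covariates intervention group and LOC".

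The Sample size section {14} plans for SSI rates of 4% and 16% and states: "A drop-out rate of about 20% is expected in this study". This raises the target from 232 to 290 patients.

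**The concern.** An imputation model should contain every term whose effect the analysis estimates. Here the analysis estimates the difference between arms, and the arm is the one term of interest that the listed imputation predictors lack. Randomisation balances the nine covariates in expectation, so they cannot carry the treatment effect into the imputed values. Both arms are filled in from a common covariate-specific risk, and the completed data show a smaller difference than the observed data.

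This happens even when data are missing completely at random, where simply analysing the observed patients would be unbiased. The primary estimate and its power are at stake, as are the supportive ITT models that reuse the imputed values. If the interim look applies the same rule, the diluted estimate would also enter the futility assessment and the sample-size re-estimation. The article does not say whether it does.

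**Working it through.** **Inputs.** From Sample size {14}: rates 4% and 16%, one-sided 2.5%, 80% power, two looks, bounds 2.963 and 1.969, continuity correction, 116 per arm evaluable, 145 per arm recruited, drop-out about 20%. From {20a}: the imputation rule. Assumption: a share *m* of endpoints is imputed in each arm, missing completely at random. The documents do not give *m*, so 5% to 20% is shown.

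**1. The plan's own figure.**
- Fixed design, unpooled variance: n = (1.960 + 0.842)² × (0.16×0.84 + 0.04×0.96) / 0.12² = 94.19 per arm.
- Group-sequential inflation factor 1.056: 94.19 × 1.056 = 99.46.
- Continuity correction: 99.46/4 × [1 + √(1 + 4/(99.46×0.12))]² = 115.5, so 116 per arm and 232 in all.
- Drop-out: 232/0.8 = 290.
- The O'Brien-Fleming-type spending function gives efficacy bounds 2.963 and 1.969.

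The stated sample size and efficacy bounds reproduce.

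**2. Dilution.** Without an arm term, imputed patients in both arms take on average the pooled observed rate, (4% + 16%)/2 = 10%.
- Experimental: (1 − m)×4% + m×10%
- Control: (1 − m)×16% + m×10%
- Difference: (1 − m)×12 points

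| m | Experimental | Control | Difference |
|---|---|---|---|
| 5% | 4.3% | 15.7% | 11.4 points |
| 10% | 4.6% | 15.4% | 10.8 points |
| 15% | 4.9% | 15.1% | 10.2 points |
| 20% | 5.2% | 14.8% | 9.6 points |

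Unequal missingness dilutes too. With 10% missing in one arm and 20% in the other, the difference is 10.2 points.

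**3. Power.** Simulation: 145 per arm, 4,000 trials, 30 imputations, Rubin's rules on the risk difference, rejection at the final bound 1.969. Baseline covariates are left out because they are balanced by randomisation.

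| m | Without arm term | With arm term |
|---|---|---|
| 5% | 92% | 93% |
| 10% | 88% | 92% |
| 20% | 77% | 89% |

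A further run gave 83% against 90% at 15% missing. Without the arm term, power was 82% at 17% and 80% at 18%, so the 80% line is crossed at about 17–18%. With the arm term the mean estimate stays at about 12 points throughout.

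These powers sit above the planned 80% because the simulated test has a single final look and no continuity correction. With a continuity correction in the test, a separate simulation gave 84% against 89% at 10% missing and 68% against 85% at 20%. On that basis the 80% line is crossed somewhere between 10% and 20% missing.

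**4. Type I error.** With 10% SSI in both arms and 20% missing, the rejection rate was about 1.0% without the arm term and 2.1% with it, against a nominal 2.5%. There is no inflation.

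**The case against.** **The list may not be exhaustive.** The text says that the models include these variables, not that they contain nothing else. All nine are baseline or operative covariates, so they can be read as auxiliary predictors with the arm taken for granted. The article is condensed, and the analysis plan may add the arm or impute by arm. This stands to the extent that a reader cannot conclude that the authors decided to leave the arm out. It does not remove the point: the article does not defer the choice of predictors but gives a specific list, and it names the intervention group where it wants that term, in the supportive model.

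**20% is not a stated share of missing endpoints.** A reader might infer that a fifth of the endpoints will be imputed and that the trial therefore has 77% power. The documents do not support this. The 20% is a drop-out allowance. Deaths are set to SSI and not imputed. An SSI documented at an earlier visit already settles the endpoint. The follow-up section {18b} provides visit windows, a form for the treating physician and a telephone fallback, and {20a} expects the endpoint for most patients. Nor does the protocol say whether the 20% covers patients excluded after randomisation. So 20% serves only as an upper bound, and at 5% missing the cost is about one point of power.

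**The error is conservative.** A reader might infer that the imputation threatens the validity of a positive result. It does not: the bias is towards no difference, and type I error is not inflated.

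**Earlier visits.** Using SSI status at day 5 and day 10 as an auxiliary predictor would be good practice. Its absence from the list is not an error in the plan.

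**Conclusion.** The point holds in limited form. The listed imputation predictors omit the intervention group, and no section provides for imputation by arm. Applied literally, the rule dilutes the primary difference and the supportive ITT estimates by about the share of endpoints imputed. Over an assumed 5% to 20%, the loss is 0.6 to 2.4 of the planned 12.0 points. Power falls by about 1 percentage point at the lower end and about 12 at the upper end. It drops below 80% only above roughly 17–18% missing when the test has no continuity correction, and earlier if it has one.

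These figures rest on the planning rates, data missing completely at random, equal missingness in the two arms and a single final look. The consequence is lost power and an understated effect, not false positives.

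**What to change.** Add one sentence to {20a} and carry it into the analysis plan: in addition to the listed covariates, the imputation model includes the intervention group, or imputation is done separately in each arm. Of the two, a single model with an arm term is likely to be easier to fit. At the planned rate the experimental arm yields only about 145 × 4% = 5.8 infections, few for a separate logistic model with nine predictors.

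Optionally, add SSI status at the last completed visit (day 5 or day 10) as an auxiliary predictor; the visit schedule already collects it.

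The cost is one sentence and one model term, with no additional patients or data. It should be settled before any unblinded analysis, including the interim look, because a later change to the primary imputation model could appear data-driven.

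### The predictors listed for imputing missing SSI omit the randomised arm, so the treatment difference shrinks by the imputed fraction; the 80% power is lost only above roughly 12% to 17% imputed

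*Protocol article*

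**What the plan says.** Section {20a} of the protocol article counts deaths before day 30 as SSI and sends every other missing primary outcome to "multiple imputations based on binary logistic regression models including LOC, ASA, BMI, age, diabetes, type of surgery, duration of surgery, use of wound-edge protectors". Glove change during the operation completes the list. That makes nine predictors, and the intervention group is not one of them.

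Section {20c} repeats the approach ("Multiple imputations will be used for missing primary endpoint data") and adds no predictor. Section {20b} runs the supportive ITT analyses "using multiple imputations for any missing SSI values". In that section the arm is named explicitly as a covariate of the supportive logistic model.

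Section {14} sizes the trial "Assuming SSI rates of 4% and 16% for the experimental and the standard group respectively". It states that the test "will have overall 80% power to show superiority of the experimental over the standard arm" with 116 evaluable patients in each arm, 232 in all. It adds "A drop-out rate of about 20% is expected in this study", which raises enrolment to 290.

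**The concern.** The arm is the variable that the primary test compares. If the imputation model lacks it, missing patients in both arms receive about the same average risk, because the listed covariates differ little between randomised groups. The imputed part of the data then carries no treatment effect. Three things follow:

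- The estimated difference is pulled towards zero.
- Rubin's variance no longer matches the sampling variation of the estimate.
- Part of the protection bought by raising enrolment from 232 to 290 is given back.

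The supportive ITT models use the same imputations and inherit the problem.

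**Working it through.** **Inputs.** From {14}: SSI rates 16% and 4%, one-sided 2.5%, two looks, efficacy bounds 2.963 and 1.969, interim futility bound 0.555, continuity correction, 116 evaluable and 145 enrolled per arm. From {20a}: the predictor list. The imputed fraction f is not stated, so it is varied.

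**1. The plan's own figures.** The O'Brien-Fleming spending function at half information gives bounds 2.963 and 1.969, as printed. The fixed-design size with unpooled variance is (1.960 + 0.842)² × (0.16×0.84 + 0.04×0.96) / 0.12² = 7.849 × 0.1728 / 0.0144 = 94.2 per arm. The two-look design with the futility bound inflates this by 1.055 to 99.4. The continuity correction n/4 × [1 + √(1 + 4/(n×0.12))]² then gives 115.5. Correcting first and inflating second gives 116.3; pooled variance gives 118.4 to 119.2. The stated 116 is reproduced within 3%, and 232/0.80 = 290.

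**2. Size of the shrinkage.** Assume equal, random missingness in both arms. Without the arm, the average imputed risk in both is (16% + 4%)/2 = 10%. Then:

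- control: 16(1 − f) + 10f
- experimental: 4(1 − f) + 10f
- difference: 12(1 − f)

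This gives 11.4 points at f = 5%, 10.8 at 10%, 10.2 at 15%, and 9.6 at 20% (14.8% against 5.2%).

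**3. Power.** Simulation with 145 per arm, 20 imputations, Rubin's rules and a pooled-variance z tested once against 1.969. The continuity correction subtracts 1/145 from the difference. Each cell shows plain z / continuity corrected.

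| Imputed | Arm omitted | Arm included |
|---|---|---|
| 5% | 92% / 88% | 93% / 90% |
| 10% | 88% / 82–83% | 92% / 89% |
| 15% | 83% / 76% | 90% / 86% |
| 20% | 76% / 68% | 88% / 84% |

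Without the arm, power passes below 80% at roughly 12% imputed (corrected) to 17% (plain).

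**4. Do the other covariates help?** LOC was added to the arm-free model, with assumed strata of 60/25/15%. At 20% imputed the difference is still 9.6 points and power still 76% / 68%.

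**5. Standard error and type I error.** At 20% imputed without the arm, the mean Rubin standard error is 0.0386 and the actual SD of the estimate is 0.0311. The ratio is 1.24, so the standard error is about 24% too wide. With no true effect, the plain test rejects in about 0.8% of trials.

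**The case against.** **The list may be open.** The word before the predictors does not close the list, the plural for the models could cover fitting per arm, and a fuller protocol or SAP may add the arm. This is a fair caution, but nothing in the text says so. Section {20b} names the arm where it is meant to be in a model. An analyst who follows {20a} as printed would impute without it.

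**A reader might infer that the trial loses its 80% power.** The document does not support that as a flat statement, because it does not show that the whole 20% drop-out is imputed:

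- {20a} expects SSI data for most patients and counts deaths as SSI.
- {11d} and the Visit 2 text in {18a} exclude some patients after surgery, and {11b} allows excluded patients to be replaced.
- {18b} provides visit windows, a form for an outside physician and a telephone fallback.
- An SSI recorded on day 5 or 10 already settles the endpoint.

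At 5% to 10% imputed, power stays above 80%. This objection stands and limits the claim.

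**A reader might also infer a distorted interim decision.** Sections {8} and {21b} tie the interim to patients who have reached the endpoint, so there may be little to impute. The share missing at that look is not stated, no interim effect can be sized without assuming one, and the futility bound is non-binding.

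**The error is conservative.** That is correct: no false claim of benefit arises from it. The estimate is still attenuated whenever anything is imputed.

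**Covariate balance is not guaranteed.** Randomisation takes place before fascial closure by a team that cannot be blinded, so glove change and duration of surgery can follow it. This qualifies the phrase same average risk but does not put the arm into the model.

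**Conclusion.** The point holds, with its size conditional on how many outcomes are imputed. As printed, the imputation rule biases the primary difference towards zero by the imputed fraction, makes the standard error too wide and the test conservative. At 20% imputed, the protocol's own drop-out figure taken as an upper case, adding the arm recovers about 12 points of power (plain, 76% to 88%) or 16 points (corrected, 68% to 84%). The stated 80% is lost only if about 12/20 = 60% (corrected) to 17/20 = 85% (plain) or more of the expected drop-out is imputed.

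These figures assume equal, random missingness in both arms, the planned 16% and 4%, 145 per arm, and a single final test without interim stopping.

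**What to change.** In {20a}, add the randomised intervention group to the predictors of the imputation model, or state that imputation is done separately within each arm. Apply the same rule at any look where outcomes are imputed and in the supportive ITT analyses of {20b}. Masked arm codes (A/B) keep the final statistician blinded. The cost is one clause in the protocol or SAP and one extra term in the imputation code, with no new data and no additional patients.

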### Interim analyses {21b}

Thirty days after the first half of the patients has reached the primary endpoint, an interim analysis will be performed by a second statistician, who does not take part in the final study analysis. A decision will be made by the study leadership, using the blinded results to stop the study with proven efficacy, stop the study for futility, continue the study as planned, or continue the study after adjusting the sample size.

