**Methods:**

PAISI is a prospective, randomized, observer- and patient-blinded, monocentric, two-arm surgical study in an adaptive parallel groups design, comparing peritoneal and wound irrigation with NaOCl/HOCl (50/50ppm) solution to irrigation with Ringer’s solution. The primary endpoint of the study is the SSI rate within 30 days postoperatively. Since there is no data on incidence rates from randomized clinical trials, the rates for sample size calculation were estimated according to the clinical experience at our institution. Therefore, the study design includes one unblinded look at the data by a second statistician, which will be performed after half of the patients reached the primary endpoint. This interim information will be used to check the assumptions and if needed, the sample size will be adjusted. The O’Brien-Fleming spending function is used to determine the efficacy test boundary and the non-binding futility boundary. The one-sided *z*-test (Group sequential test of two proportions) at the 2.5% significance level with a total of two looks at the data will have overall 80% power.

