	**…or the infection is diagnosed by the attending surgeon**

### Trial design {8}

This is a prospective, randomized, controlled, observer and patient-blinded, single-centre, two-arm surgical study with an adaptive parallel groups design. Pre-screening of potential patients (evaluation of inclusion and exclusion criteria) is possible up to 14 days prior to the planned procedure. Patients can be included if inclusion and exclusion criteria apply and written informed consent is provided. Included patients are randomized to peritoneal and epifascial wound irrigation with NaOCl/HOCl (50/50ppm) or Ringer solution. A reduction of 30-day postoperative SSI I–III rates by lavage with NaOCl/HOCl solution is postulated. Since there is currently no data on incidence rates from randomized clinical trials, the rates for sample size calculation were estimated according to the clinical experience at our institution. Therefore, the study is designed with one unblinded look at the data, which will be performed after half of the patients reached the primary endpoint (30 days post-surgery), by a second study statistician, who will not participate in the final study analysis. This interim information will be used to check the assumptions which were used to calculate the sample size for the study. If needed, the sample size will be adjusted.

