## Assignment of interventions: blinding

### Who will be blinded {17a}

The blinding procedure is restricted to participating patients, the statistician who performs the final analysis and the outcome assessors. Blinding of the surgical team that performs the intervention is impossible because of the distinctive smell of NaOCl/HOCl solution. Postoperatively, an outcome assessor of the local study group, who is unaware of the patient’s intraoperative intervention, will clinically assess the primary endpoint (SSI) on 3 postoperative study visits.

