## Oversight and monitoring

### Composition of the coordinating Centre and trial steering committee {5d}

As this study is planned as a monocentric trial, there is no coordinating centre. The trial steering committee in this setting consist of the study leadership (principal investigator, deputy investigator and coordinating investigator) which is responsible for recruitment of patients and data management. The statistical analysis will be performed by an independent statistician. Trained medical doctors of the local study group will take informed consent. The study leadership will meet once a month to discuss progress and problems regarding the trial. Following the planned interim analysis after 50% of patients are recruited a meeting with the trial statistician and the scientific advisors as well as the funders will be held to discuss the results and consequences. The ethics committee will be informed about the outcome of this meeting. Public involvement is not planned in this study.

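### The interim rule has the study leadership decide on blinded results, although the look is unblinded and the bounds need the between-arm Z; what leaves the second statistician should be fixed as a recommendation only

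*Protocol article*

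**What the plan says.** **The look.** The abstract states that "the study design includes one unblinded look at the data by a second statistician". Trial design {8} repeats that "the study is designed with one unblinded look at the data" and adds that this second statistician takes no part in the final analysis.

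**The decision.** Interim analyses {21b}: "A decision will be made by the study leadership, using the blinded results to stop the study with proven efficacy". The sentence goes on to futility, continuing as planned, and continuing with an adjusted sample size.

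**The bounds.** Sample size {14} gives interim bounds of 2.963 (efficacy) and 0.555 (futility, non-binding) on the Z scale of a one-sided test of two proportions.

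**The recipients.** Section {5d} defines the leadership as the principal, deputy and coordinating investigators, who are responsible for recruitment and data management. After the interim analysis, "a meeting with the trial statistician and the scientific advisors as well as the funders will be held to discuss the results and consequences". Section {21a} plans no data monitoring committee.

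**Who stays blinded.** Section {17a}: "The blinding procedure is restricted to participating patients, the statistician who performs the final analysis and the outcome assessors".

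**The trigger.** Three wordings appear:
- Sample size {14}: "an interim analysis is planned after half of the patients have reached 30 days post-surgery" (Trial design {8} agrees).
- Interim analyses {21b}: "Thirty days after the first half of the patients has reached the primary endpoint".
- Section {5d}: "Following the planned interim analysis after 50% of patients are recruited".

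**The concern.** The article says who makes the interim decision and on what kind of data, but the kind of data it names does not fit the rule it sets. Efficacy and futility are judged on a comparison between arms, and results in which the arms cannot be told apart do not contain that comparison.

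If the word blinded is read loosely, so that the leadership sees results by arm or by coded arm, the rule can run, but the people who recruit patients and manage the data then know the interim effect during the second half. The {5d} meeting takes the same results to advisors and funders.

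At stake are whether the trial's only stopping and sample-size decision can be carried out as written, and whether the second half is protected from knowledge of the first. The surgical team already knows each allocation ({17a}), and Table 1 accepts an infection diagnosed by the attending surgeon. Knowledge of an interim trend therefore has at least one possible route to the endpoint.

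**Working it through.** **1. The plan's own figures.** Inputs from Sample size {14}: 4% v 16%, one-sided alpha 0.025, power 80%, two looks at information fraction 0.5, continuity correction.
- O'Brien-Fleming-type spending at t = 0.5: 2[1 − Φ(z(1−0.025/2)/√0.5)] = 0.001525. This gives an interim bound of 2.963 and a final bound of 1.969. Both match.
- Non-binding beta spending with beta = 0.20 spends 0.0699 at the interim. The final drift is 2.879, so the interim mean is 2.879 × √0.5 = 2.036. The futility bound is Φ⁻¹(0.0699) + 2.036 = 0.559, against 0.555 stated.
- Unpooled fixed n of 94.2 per arm × 1.056 = 99.5; continuity corrected 115.5, so 116 per arm and 232 in total. Match.

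The design is therefore built on the arm-wise Z. The interim decision matters: the chance of crossing 2.963 under the planned rates is 1 − Φ(2.963 − 2.036) ≈ 18%, and the chance of falling below the futility bound with no effect is Φ(0.559) ≈ 71%.

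**2. Reading A: blinded means pooled.** The pooled rate under the planned effect is (4% + 16%)/2 = 10%, the same as under 10% v 10%. At half of 232 there are 58 patients per arm, and 58 × (0.04 + 0.16) = 11.6 infections are expected. Take 12 in 116, with Z = (difference in rates)/√[p(1 − p) × 2/58] and p = 12/116 (pooled variance, no continuity correction). The denominator is 0.0566.

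| Experimental v control | Z | Decision |
|---|---|---|
| 1 v 11 | 3.05 | efficacy |
| 2 v 10 | 2.44 | continue |
| 4 v 8 | 1.22 | continue |
| 6 v 6 | 0.00 | futility |

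One pooled total is compatible with every outcome of the rule.

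**3. Reading B: coded arms.** The test is one-sided, so direction is needed and a masked label withholds it. Under the planned effect the totals would be about 58 × 0.04 = 2.3 and 58 × 0.16 = 9.3, so the size of the difference is visible in any case. Surgeons know the allocation of their own patients, so the code could be guessed.

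**4. Reading C: results by arm.** The rule works, but {21b} and {5d} together place the effect with the recruiting investigators, the advisors, the funders and a statistician whom {5d} does not identify further.

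**5. The trigger.** Assume 10 patients a month (Recruitment {15}), 20% drop-out and a final 232.
- Half at day 30: 116/232 = 0.50.
- Thirty days later: (116 + 10 × 0.8)/232 = 124/232 = 0.53.
- Half of 290 recruited, with the last month's 10 not yet at day 30: (145 − 10) × 0.8/232 = 108/232 = 0.47.

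With 2.963 and 1.969 held fixed, the one-sided type I error is 1 − P(Z1 < 2.963, Z2 < 1.969), with correlation √t:

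| t | 0.40 | 0.50 | 0.60 | 0.69 |
|---|---|---|---|---|
| Type I error | 2.52% | 2.50% | 2.48% | 2.46% |

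This range covers all three wordings.

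**The case against.** The strongest reply is that an unblinded analyst with blinded recipients is an ordinary firewall. The second statistician could apply the bounds and hand the leadership a masked result or a bare recommendation, and the {5d} meeting could discuss only that. The article does not exclude this reading, so a reader should not infer that the rule must either fail or unblind the trial. What remains is that {21b} speaks of results, {5d} has results discussed, and neither limits them to a recommendation.

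Other points count against a stronger claim:
- The trial statistician at the meeting may be the second statistician. A conflict with {17a} arises only if it is the one who does the final analysis, and the text does not say.
- Independent blinded assessors examine the wounds ({17a} and Visit 3 to 5), and nothing says that they attend the meeting. Randomization is online, stratified and blocked at the end of surgery, so an interim trend does not reveal the next allocation. Bias is possible, but its size is not shown.
- The trigger wordings hardly move alpha, and a spending function allows the bounds to be recomputed at the actual fraction.
- A journal article may leave the distribution of interim tables to the full protocol. That silence is no finding. The point rests on what the article does say: blinded in one place, unblinded in others, and results shared with named groups.

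**Conclusion.** The point stands as a contradiction that needs repair. As worded, {21b} either cannot carry out the stopping rule of {14} (pooled reading) or, read with {5d}, lets the recruiting investigators, the funders and possibly the final-analysis statistician learn the interim effect while the trial continues, unless a firewall exists that the text does not describe. There is no monitoring committee in between.

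The pooled reading fails outright: one total of 12 infections spans Z from 0.00 to 3.05. For the other readings the consequence is a risk of operational bias of unquantified size, reduced by the blinded assessors. A reader might infer that patients' allocations are exposed or that the blinded assessors are compromised; the documents do not support either. The trigger discrepancy is a minor matter of consistency.

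The figures assume 58 patients per arm at the interim, the planned 4% and 16%, and, for the trigger, the article's accrual and drop-out figures.

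**What to change.** **Interim analyses {21b}.** State that the second statistician computes the arm-wise Z, compares it with 2.963 and with the non-binding 0.555, applies a sample-size rule fixed in advance, and gives the leadership only a recommendation: stop for efficacy, stop for futility, continue, or continue with a changed sample size. Release no arm-level or coded arm results while the trial continues. Delete the reference to blinded results. The leadership can still decide to continue after a futility recommendation, because that bound is non-binding.

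**Sample-size change.** A precise new total can let the effect be back-calculated. Give it in coarse pre-set steps, or withhold the rule from the leadership.

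**Section {5d}.** The meeting discusses the recommendation, not the comparative results. Say which statistician attends, and that the final-analysis statistician stays blinded.

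**Trigger.** Use one wording in {8}, {14}, {21b} and {5d}: the point at which half of the planned patients have reached day 30 after surgery. Handle deaths and missing outcomes as in Statistical methods {20a} (death counts as infection, other missing values imputed), so that no separate definition of evaluable is needed.

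**Cost.** Wording only, using the second statistician already planned; no extra patients and no new committee. The downside is that the leadership and funders do not see interim rates.
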